#### Data collection

Rolling enrollment has been adopted, making the data collection periods tailored to each individual in the study. Data are being collected at baseline (i.e., one week prior to the start of the intervention); six weeks into the intervention; immediately post-intervention (i.e., three months); and six months post-intervention. All data is being entered electronically at the host university, on a secure server. Consent and other written forms are stored and locked in a secure drawer, in a locked office, at the host university. In order to maintain confidentiality and anonymity, participants are assigned a unique identification code upon registering in the study. Participant files will be kept in storage for up to 5 years after completion of the study. Baseline and follow-up assessments are conducted at the host university or at the participant’s home by the lead researcher and a research assistant. An email link is sent to parent participants asking them to complete the questionnaires, and email and telephone reminders are conducted one and two weeks later if no response is received. If there is no response, it is assumed that the participant has missed the data collection time and contact re-commences at the next follow-up time. If a participant cannot be contacted after three consecutive communication attempts, it is assumed that they are lost-to-follow-up. A grocery store gift card is provided to participants who complete the study. An overview of study measurements and time points can be found in Table 1.

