### Data analysis

SPSS (version 24) will be used to conduct a repeated measures MANCOVA to assess differences within groups, and a two-way ANCOVA to assess differences between groups, where baseline data will be the covariate, with differences analyzed using the post-hoc Least Square Differences method. As socioeconomic status (SES) has an impact on nearly all health issues, including obesity, and understanding its impact in the proposed project is necessary, a general linear model utilizing SES as covariate will be completed. Classification for SES will be based on education and low income cut off scores (LICO) utilizing Statistics Canada’s definition. The semi-structured interview responses from parents, to determine changes in family health behaviours and overall program experiences, will be analyzed in NVivo by two independent researchers. Inductive content analysis (a method in which patterns, themes, and categories emerge from the data, without an existing framework; [76]) will be employed to identify feedback themes. This process involves open coding, in which data is read through several times, and as many headings as necessary are written down to describe all aspects of the content [77]. The headings are then collected on a coding sheet, and categories are grouped and sorted into higher order headings [78, 79]. Data are classified into groups in order to help describe a phenomenon, increase understanding, and generate knowledge [80]. Once categories are decided upon, the two researchers compare headings and come to consensus on final themes, with the support of NVivo software.

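### The only covariate named alongside the within-group MANCOVA is baseline; if it is used there, the model does not soundly test change from baseline

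*Protocol article*

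**What the plan says.** The Data analysis section of the protocol article gives two jobs to two models in one sentence: a "repeated measures MANCOVA to assess differences within groups, and a two-way ANCOVA to assess differences between groups, where baseline data will be the covariate". The sentence ends "with differences analyzed using the post-hoc Least Square Differences method". A third analysis follows separately: "a general linear model utilizing SES as covariate will be completed". The software is SPSS version 24.

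The Data collection section sets four measurement times: baseline, one week before the start, and then "six weeks into the intervention; immediately post-intervention (i.e., three months); and six months post-intervention". Counted from the start, the last visit falls at 3 + 6 = 9 months.

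The article does not say whether baseline is also a level of the time factor in the MANCOVA, or whether any covariate is centred.

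**The concern.** A MANCOVA needs a covariate, and baseline is the only one the sentence offers. Baseline adjustment suits the comparison of two randomised arms at follow-up. It does not suit a test of change over time within an arm, because there baseline is the reference point for the change.

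The model can be set up in two obvious ways.

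- **Follow-ups only.** Baseline is the covariate and the time levels are 6 weeks, 3 months and 9 months. The time effect then compares follow-ups with one another. A gain made by week 6 and kept does not show in it.
- **Baseline twice.** Baseline is both the first time level and the covariate. The omnibus time test is then a test of the intercept when change is regressed on baseline, that is, the expected change for someone with a baseline of zero. For BMI such a person cannot exist; eligibility requires more than 25 kg/m².

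At stake is what the trial reports about whether parents and children in each arm changed. Depending on the outcome, the analysis could report change where there is none or miss change that occurred.

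**Working it through.** **The plan's own figure.** 50 dyads at 1:1 give 25 per arm. With d = 0.8 and two-sided alpha 0.05, the two-sample t-test (noncentral t) has power 79.1%, against 79% stated. That figure concerns the between-group comparison and is reproduced.

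**Inputs for the within-group check.** From the article: four visits and 25 per arm. Assumed, because the article gives no outcome means, SDs or correlations: mean/SD of 7500/2500 (steps-like) and 32/5 (BMI-like); equal correlations between visits of 0.5, 0.7 or 0.9, or a correlation that decays as 0.9 per month.

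**Why the test at zero misleads.** With mean μ, constant SD, correlation r and no true change, the regression of (follow-up − baseline) on baseline has slope r − 1 and intercept μ(1 − r). Regression to the mean alone makes this intercept non-zero:

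- 7500 × (1 − 0.5) = 3750 steps; 7500 × (1 − 0.9) = 750 steps
- 32 × (1 − 0.5) = 16 BMI units; 32 × (1 − 0.9) = 3.2 BMI units

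A real change can also be cancelled. With BMI 32, r = 0.97 and a true fall of 0.8, the intercept is 32 × 0.03 − 0.8 = 0.96 − 0.80 = 0.16, close to zero.

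**Simulated rejection rates for the omnibus time test, no true change** (multivariate Hotelling test in one arm of 25, nominal 5%, 4000 runs per setting; ranges cover the two mean/SD pairs):

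| Model | r = 0.5 | r = 0.7 | r = 0.9 | decaying |
|---|---|---|---|---|
| Baseline as level and raw covariate | 77–80% | 46–48% | 16–17% | 65–69% |
| Same, covariate centred | 7–9% | about 7% | about 5% | 7–8% |
| Follow-ups only, raw covariate | about 5% | about 5% | about 5% | 47–51% |
| Four visits, no covariate | 4–5.5% | about 5% | about 5% | about 5% |

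**Why centring leaves a small excess.** The model's error variance for mean change is proportional to 1 − r², while the actual variance of mean change is proportional to 2(1 − r). The ratio is (1 + r)/2, which is 0.75 at r = 0.5 and 0.95 at r = 0.9. The standard error is therefore slightly too small.

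**Real change present.**

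- Follow-ups only, sustained 0.6-SD gain from week 6 (steps 8000/3000, r = 0.6): detected about 5% of the time, centred or not. With baseline as a level and no covariate: about 90%.
- Baseline as level and raw covariate, BMI 32/5, r = 0.97, fall of 0.8: power 5%, against 87 to 88% without the covariate.
- Four visits, no covariate, sustained 0.8-SD change: power 98 to 100%.

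**The case against.** The strongest reply is that the baseline clause directly follows the between-group ANCOVA, where it is standard and correct, and may apply only there. That is possible, and the text does not settle it. The MANCOVA then has no covariate, and the sentence needs correcting for that reason instead.

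A reader might infer that the within-group P values are simply wrong. The article does not support that.

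- The high error rates need four things together: baseline as a level, baseline as covariate, no centring, and reliance on the omnibus time test. The plan also names post-hoc LSD comparisons. These are normally made on adjusted means at the covariate mean, where the false-positive rate for 3 months against baseline is about 7 to 8%. For the BMI example, power is then 89% with or without the covariate.
- With follow-ups only and equal correlations, the P value is valid. It answers a different question.

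A reader might also extend the point to SES, arguing that an uncentred code would test time at SES = 0. That is speculative: SES belongs to a separate model, its coding is not given, and no time test in that model is described.

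Finally, the article is a condensed account, and details such as centring may stand in a fuller document. That is fair for centring. It does not cover the pairing of method and covariate, which the article itself states. What stands of the objection is that the point is conditional and its consequences are limited.

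**Conclusion.** The sentence should be corrected. On its natural reading, the model given for within-group differences either leaves change from baseline untested (about 5% detection of a sustained 0.6-SD gain) or, if baseline is also an uncentred covariate, has an omnibus error rate of about 16 to 80% against a nominal 5%, for assumed correlations of 0.9 to 0.5 with 25 per arm. With centring, or with LSD comparisons at the covariate mean, the error is about 7 to 8% at correlations of 0.6 to 0.7, and 5 to 9% across all settings tried. These sizes rest on assumed means, SDs and correlations and on baseline being the MANCOVA covariate.

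It would be too strong to say that the trial's conclusions are at risk. The directional hypotheses on coaching plus education against education alone, and the sample size, concern the comparison between arms. The baseline-adjusted ANCOVA for that comparison is sound, and the 79% power stands. Within-arm change is not the randomised comparison, so this ranks below an essential correction.

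**What to change.** In the Data analysis section, state that baseline is the covariate in the between-group model only. For within-group change, enter all four visits as the repeated response, with baseline as a time level and no baseline covariate, and report change from baseline in each arm with a 95% CI. A repeated-measures model or a mixed model will serve; a mixed model is not required to cure this defect. If any other continuous covariate enters a model in which a time effect is tested, centre it at its sample mean first.

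The cost is a change of wording. No new data are needed, and the named software can fit either model.

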**Methods:**

Using a randomized controlled trial design, the researchers aim to identify the impact of coaching plus education (intervention) compared to education only (control) on parents with overweight/obesity and their children (ages 2.5–10, of any weight). A total of 50 dyads are being recruited and randomly assigned using a 1:1 ratio into the control or intervention group. The control group receive 6 webinar-based education sessions focused on physical activity and nutrition. The intervention group receive the same education sessions and nine, 20-min telephone-based sessions with a certified coach. Coaching and health education sessions are conducted with the parent/guardian of the dyad. This paper provides a detailed methodological account of this program.

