#### Sample size and eligibility criteria

A sample size calculation was conducted using the Horatio Computer Software program [57]. The inclusion of 50 parent-child dyads was deemed sufficient to detect a large effect size (d = 0.8) of a two-level, between groups independent variable, 79% of the time, using a 0.05 alpha level.

To be eligible for this study, parents/guardians must have a BMI of > 25 kg/m^2^, live with their child (aged 2.5–10) for at least 5 days of the week, speak English, and are comfortable using a computer for data collection purposes. Because adolescence spans 10–19 years [58], the research team decided targeting children aged 10 and under for the study described in this paper would be the most impactful. If there are two parents and two children in a family who meet the inclusion criteria, they are permitted to participate as two separate dyads. In the case where two parent-child pairs within the same household are both randomized to receive the intervention, the parents will work with two different coaches.

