### Measures

At baseline, the parent participant is asked to complete demographic information forms on behalf of themself and their child. Both groups complete the same assessments at each follow-up period and these consist of BMI (height and weight), waist circumference, step count, dietary intake, standardized and previously validated measures (a detailed list is included below), and open-ended questions to glean parents’ perceptions of how the intervention is impacting them and their child (any domain the parent chooses to discuss).

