### Primary outcome measures

#### 7-day step count

Yamax Digi-Walker SW-650 pedometers are provided to participants (for both parent and child), as this model is used frequently in research [59, 60]. The Digi-Walker SW-650 records steps, calculates distance travelled based on individual stride length, and has a stopwatch. For the purpose of this study, only step-count data are recorded. Participants are asked to wear the pedometer for all waking hours except when swimming or bathing, and to reset it to zero each morning, over the course of one week (7 days; [59]) at all measurement time points.

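### The between-group models for child step count and child diet do not adjust for the child's age, although ages run from 2.5 to 10; adding it is a cheap, modest gain, mainly for diet

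*Protocol article*

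**What the plan says.** The Data analysis section of the protocol article names the adjustment for the between-group comparison: "a two-way ANCOVA to assess differences between groups, where baseline data will be the covariate". It adds a general linear model with SES as covariate and gives a reason for that choice. Child age is not named as a covariate anywhere.

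Eligibility requires that parents "live with their child (aged 2.5–10) for at least 5 days of the week", so children range from 2.5 to 10 years. Under Study purpose, child step count and child 24 h dietary intake are listed among the primary outcomes. Study design describes blocked randomisation and mentions no stratification by age. The abstract has 50 dyads "randomly assigned using a 1:1 ratio into the control or intervention group", which gives about 25 children per arm.

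Age must be known at screening. In addition, according to the Measures section, "the parent participant is asked to complete demographic information forms on behalf of themself and their child".

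**The concern.** Over so wide an age range, a child's steps and intake may well depend on age, and in a trial of this size the arms can differ in mean age by chance. A baseline measurement carries some of the age information, but only as much as its correlation with follow-up allows. Where the baseline is noisy, part of an age-driven difference between arms stays in the estimated coaching effect, and age-related variation stays in the residual error. Age is known for every child at entry, so the plan may be giving up precision on two child outcomes that it calls primary. Adding age later, after an imbalance has been seen, would be a data-driven choice open to challenge.

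**Working it through.** **1. The plan's own figure.** The sample size section specifies "a large effect size (d = 0.8) of a two-level, between groups independent variable", detected "79% of the time, using a 0.05 alpha level". With 25 per arm the noncentrality is 0.8/√(2/25) = 2.83 on 48 df. A two-sided two-sample t-test then has power 79.1% (normal approximation 80.7%; one-sided t 87.4%). The stated 79% is reproduced. It assumes no covariate, so the choice of covariates does not affect it.

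**2. Size of a chance age gap.** Assumption: ages uniform on 2.5 to 10.
- SD = 7.5/√12 = 2.17 years.
- SE of the difference in mean age = 2.17 × √(2/25) = 0.61 years, or 0.283 SD.
- 95% limit = 1.96 × 0.61 = 1.20 years, or D = 0.554 SD.

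**3. What baseline adjustment leaves.** Scale the outcome to variance 1 at each visit. Let a be its correlation with age, taken as equal at both visits, and r the baseline-to-follow-up correlation. An age gap of D SD shifts baseline and follow-up by aD each. ANCOVA on baseline has slope r, so aD − r·aD = a(1 − r)D remains. The share left is 70%, 50% and 30% for r = 0.3, 0.5 and 0.7. At the 95% limit D = 0.554, with the SE of the treatment difference √(2/25 × (1 − r²)):
- r = 0.3, a = 0.5: 0.5 × 0.7 × 0.554 = 0.19 SD (SE 0.27).
- r = 0.5, a = 0.3: 0.3 × 0.5 × 0.554 = 0.08 SD (SE 0.25).
- r = 0.7, a = 0.3: 0.3 × 0.3 × 0.554 = 0.05 SD (SE 0.20).

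**4. What adding age gains.** Residual variance is 1 − r² with baseline only, and 1 − R² with baseline and age, where R² = (r² + a² − 2ra²)/(1 − a²). For r = 0.5, a = 0.3: R² = (0.25 + 0.09 − 0.09)/0.91 = 0.275, so residual variance falls from 0.750 to 0.725, a cut of 3.3%. The net column multiplies the variance ratio by 45/44, an approximate charge for estimating one more coefficient. Power is at d = 0.8 from the noncentral t with 47 and 46 df, 25 per arm and no dropout. It allows for the lost degree of freedom but not for the 45/44 factor.

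| r | a | Residual variance, baseline only | With age | Cut | Net cut | Power, baseline only | With age |
|---|---|---|---|---|---|---|---|
| 0.3 | 0.1 | 0.910 | 0.905 | 0.5% | −1.7% | 82.7% | 82.9% |
| 0.3 | 0.2 | 0.910 | 0.890 | 2.2% | 0.0% | 82.7% | 83.5% |
| 0.3 | 0.5 | 0.910 | 0.747 | 17.9% | 16.1% | 82.7% | 89.3% |
| 0.5 | 0.3 | 0.750 | 0.725 | 3.3% | 1.1% | 89.2% | 90.2% |
| 0.5 | 0.5 | 0.750 | 0.667 | 11.1% | 9.1% | 89.2% | 92.4% |
| 0.7 | 0.1 | 0.510 | 0.509 | 0.2% | −2.1% | 97.2% | 97.3% |
| 0.7 | 0.3 | 0.510 | 0.501 | 1.7% | −0.5% | 97.2% | 97.4% |
| 0.7 | 0.5 | 0.510 | 0.480 | 5.9% | 3.7% | 97.2% | 97.9% |

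At d = 0.5, power moves from 44.3% to 51.7% (r = 0.3, a = 0.5), from 51.6% to 52.9% (r = 0.5, a = 0.3) and from 67.9% to 68.6% (r = 0.7, a = 0.3).

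**The case against.** **It could be left to the analysis plan.** The article is condensed, and secondary covariates are often listed elsewhere. It never says that baseline is the only covariate, and it does not name the second factor of the two-way ANCOVA. This carries some weight. But the section does state an adjustment set and argues for one member of it, so proposing a better set is fair comment on what is written.

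**The age effect is not documented.** This stands. Nothing in the article says how strongly steps or intake vary with age between 2.5 and 10, and the diet score is not defined. If a is about 0.2 or less, there is no net gain.

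**Stronger readings that the documents do not support:**
- A reader might take the λ = 0.28 quoted for web-based recall to mean that baseline removes only 28% of an age difference. The article gives λ as an attenuation factor from a cited validation cohort. It is not a baseline-to-follow-up slope for these children, and stable misreporting by the same person would raise that slope. The figure supports calling the recall noisy and no more.
- A reader might infer that age imbalance goes largely uncorrected for both outcomes. That needs r below 0.5. It is plausible for one 24 h recall, but less so for steps recorded over seven days.
- A reader might call the remaining shift a bias. Under randomisation, chance imbalance neither biases the estimator nor invalidates the test, and its variability is already in the residual error. The shifts in step 3 are also values at the 95% limit. At the average absolute gap (0.8 × 0.283 = 0.23 SD) they fall to about 0.08, 0.03 and 0.02 SD.
- A reader might call the precision free. It costs a coefficient, and in several rows of the table that cost exceeds the gain.

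**Conclusion.** The point holds as a modest efficiency improvement. The stated between-group models omit a baseline variable that is known for every child and may be prognostic. The gain in residual variance runs from about 0.2% to 18% over r = 0.3 to 0.7 and a = 0.1 to 0.5. Both ranges are assumptions, because the documents give neither quantity. The gain is material only where age is strongly related to the outcome and the baseline is unreliable, which points to child diet more than to steps. The age-gap figures rest further on uniform ages and 25 children per arm. No figure in the plan is wrong.

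**What to change.** In the Data analysis section, add the child's age at baseline, as a continuous covariate alongside the baseline value of the outcome, to the between-group models for child step count and child dietary intake. Specify this before outcome data are examined by arm. Suggested wording: between-group analyses of child step count and child dietary intake will include the baseline value of the outcome and the child's age in years at baseline as covariates.

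The cost is one degree of freedom per model and one sentence of text. If age turns out to be only weakly related to the outcome, precision could fall by about 2% of residual variance. Randomisation, data collection and sample size need no change.

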### Study purpose

This study will explore the impact of a parent coaching intervention, with parent and child outcomes, on promoting healthy behaviours among the dyad. Specifically, this research aims to identify the impact of a coaching plus health education intervention compared to health education only on: (a) the PA levels of children (ages 2.5–10) and their parents with overweight/obesity; (b) the dietary intake of children and their parents with overweight/obesity; (c) parental motivation to engage in healthy behaviours; and (d) parental perspectives on how the program has impact on their and their child’s nutrition and PA behaviours. These primary outcomes will be measured via in-person parent interviews, parent and child 7-day step count and 24 h dietary intake, and standardized and validated questionnaires. Due to children’s active growth periods, PA and nutrition behaviours can be better predictors of health than anthropometric indicators [54]. Secondary outcomes will be measured by assessing: (a) parental BMI (calculated by measuring weight in kg, over height in m^2^); (b) parents’ overall perception of health; and (c) parents’ psychosocial variables (i.e., social support, self-esteem, and self-efficacy).

The research team hypothesizes that immediately following and at 6 months post-intervention, the coaching plus education group will report higher levels of parent-child PA, greater improvements in parent-child dietary intake choices, greater parental psychosocial benefits, and greater improvements in parents’ BMI values, compared to those who receive education only. The research team predicts that parents from higher socioeconomic status (SES) backgrounds will be impacted more favorably than those from lower SES backgrounds, as researchers have found greater difficulties associated with affecting behaviour change within lower SES environments [20]. It is also hypothesized that male parents and children will have higher PA levels, while female parents and children will have greater dietary intake improvements, and female parents’ psychosocial health will be impacted most positively, given that previous research has found young males tend to be more active than their female counterparts, and obesity affects psychosocial health of women more negatively than men [27].

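### At least six unranked primary outcomes at two time points, no multiplicity control across them, and a sample size that covers one comparison

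*Protocol article*

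**What the plan says.** **Primary outcomes.** Study purpose lists physical activity of parents and children, diet ("the dietary intake of children and their parents with overweight/obesity"), parental motivation and parental perspectives. It then calls them all primary: "These primary outcomes will be measured via in-person parent interviews, parent and child 7-day step count", followed by 24-hour dietary intake and validated questionnaires. The section Primary outcome measures gives the instruments: pedometer steps for parent and child, a 24-hour recall, the IPAQ, the TSRQ and interviews. None is ranked above the others.

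**Time points.** The hypothesis, also in Study purpose, is that "immediately following and at 6 months post-intervention, the coaching plus education group will report higher levels of parent-child PA", with matching predictions for diet and other outcomes. The six-week assessment is not part of this hypothesis.

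**Sample size.** "The inclusion of 50 parent-child dyads was deemed sufficient to detect a large effect size". The article sets that effect at d = 0.8 and gives 79% power for a single comparison of two groups. This paragraph contains the only alpha in the article, 0.05. It names no outcome and no time point.

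**Analysis.** Data analysis assigns within-group differences to a repeated measures MANCOVA and between-group differences to a two-way ANCOVA with baseline as covariate, "with differences analyzed using the post-hoc Least Square Differences method".

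**Conclusion to be drawn.** The Discussion part of the abstract says the trial will determine whether coaching plus education beats education alone. It adds that the approach may be applied more broadly if proven effective. Neither statement is tied to a particular outcome or time point.

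**The concern.** Six primary measures at two time points make at least 12 between-group tests. As written, a significant result in any of them could be reported as showing that coaching works on a primary outcome. The 5% error rate belongs to one test, but the conclusion rests on the whole set.

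The sizing and the testing also disagree. The stated power is right for a single comparison at 0.05. If error were controlled across all the primaries, the same 50 dyads would have much less power than stated. At stake is whether a headline claim of effectiveness, offered as grounds for wider public health use, carries the error rate and power that the article implies.

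**Working it through.** **Inputs from the article**
- 50 dyads, "randomly assigned using a 1:1 ratio into the control or intervention group", so 25 per arm.
- d = 0.8 and alpha 0.05. Sidedness is not stated.
- Quantitative primaries: 2 (steps, parent and child) + 2 (diet, parent and child) + 1 (IPAQ) + 1 (TSRQ) = 6. Interviews are qualitative and not counted.
- Time points in the hypothesis: 2. Tests: 6 × 2 = 12.

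**Assumptions**
- Each between-group test is two-sided at 0.05. Data analysis states no alpha, so this is carried over from the sample-size paragraph.
- The correlation between tests is not given. Independence gives the upper figure; common correlations of 0.3 and 0.5 show how far it falls.

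**Step 1. Reproduce the stated power.** Two-sample t-test, 48 degrees of freedom, noncentrality 0.8 × √(25/2) = 2.83, two-sided critical value 2.01: power 79.1%. This matches the stated 79%. A one-sided test would give 87.4%, so the calculation is two-sided and covers one comparison.

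**Step 2. At least one false positive in either direction.** For k independent tests this is 1 − 0.95^k.

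| Tests | Independent | Correlation 0.3 | Correlation 0.5 |
|---|---|---|---|
| 6 (one time point) | 1 − 0.95^6 = 26.5% | 24% | 21% |
| 12 (both time points) | 1 − 0.95^12 = 46.0% | 40% | 32% |

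The correlated figures treat the test statistics as equicorrelated normal variables, each compared with ±1.96.

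**Step 3. At least one false positive favouring coaching.** Each two-sided test allows 2.5% in that direction, so the formula is 1 − 0.975^k.

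| Tests | Independent | Correlation 0.3 | Correlation 0.5 |
|---|---|---|---|
| 6 | 1 − 0.975^6 = 14.1% | 12% | 10% |
| 12 | 1 − 0.975^12 = 26.2% | 20% | 16% |

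**Step 4. Power if all primaries are kept and error is controlled.** Same t-test, d = 0.8, no allowance for dropout.

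| Level per test | Power, 25 per arm | Per arm for 79% |
|---|---|---|
| 0.05 (one test) | 79% | 25 (50 dyads) |
| 0.05/6 = 0.00833 | 53% | 39 (78 dyads) |
| 0.05/12 = 0.00417 | 44% | 45 (90 dyads) |

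**Step 5. What LSD does here.** There are two arms, so each outcome at each time point has one between-group contrast. LSD has nothing to adjust in that contrast and does not inflate it. It also does nothing across outcomes or time points, where the inflation arises. The MANCOVA is assigned to within-group differences, so it does not act as an overall test that must be passed before the between-group tests.

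**The case against.** **An analysis plan may settle multiplicity.** A journal article can leave the detailed procedure to a document not shown here, so its absence alone would be no fault. This does not remove the point. The article itself names several unranked primaries, states a hypothesis at two time points and sizes for one comparison, and these choices do not fit together.

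**The study describes itself as exploring an effect.** Study purpose and the Discussion use that language, which tempers the seriousness. The abstract is more confirmatory, with its talk of determining effectiveness and of wider use.

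**Stronger readings that the article does not support**
- *A chance finding of effectiveness is likely.* The 46% counts errors in either direction, including results favouring education alone, and is still below one half. The figure relevant to a claim for coaching is at most 26%.
- *LSD is the cause.* Step 5 shows that it is not. An inflation of about 20% per outcome can be computed for unprotected LSD over four visits, but that compares visits, not arms. The article also does not say whether an overall test comes first, and with baseline as covariate only three follow-up visits remain.
- *There are 18 tests, with a 60% error rate.* This requires the four TSRQ factors to be tested separately. The article reports them as the structure hypothesised in a cited validation study and does not say that the trial will test each one.
- *The 79% power belongs to a particular outcome, such as parent steps.* The sample-size paragraph names none.

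**Conclusion.** The concern holds: the primary outcomes and time points are too many and too loosely ordered for a trial sized on one comparison. The error rate behind a claim that coaching is more effective is about six to ten times the single-test value in the favourable direction (16–26% against 2.5%), and about six to nine times in either direction (32–46% against 5%). These ranges rest on 12 tests, each at an inferred two-sided 0.05, and on correlations from 0.5 down to zero that are assumed, not documented. Stronger correlation would lower them. The count of 12 is a minimum, because no dietary variable is named and more than one could be tested. The stated power is arithmetically correct but describes only one of these tests.

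**What to change.** **Preferred.** Before any comparative analysis, name one primary outcome at one time point, tested at 0.05. The choice is the sponsor's. Treat the other outcomes and the other time point as secondary, either tested with Holm or reported as estimates with 95% confidence intervals. Report the interviews as qualitative findings. The 79% power for 50 dyads then applies to the named comparison, on the article's own assumption of d = 0.8.

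**Alternative.** Keep all the primaries, apply Holm across the primary between-group tests, and restate the power from step 4. Those values are at the Bonferroni level, which is Holm's first step, so Holm can only equal or exceed them.

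**Cost.** Changes of wording and a registry update; no new data under the preferred option. Fewer results can be called confirmatory. The trial is under way and was registered retrospectively, and the lead researcher knows the allocation and takes part in assessments. The record should therefore state when the choice was made and that it was made without sight of outcome data by arm.
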